**Fig. 4 Fig4:**
[figure not shown]
Map showing the boundary of Old Moat and location of all intervention sites. © Crown Copyright and Database Right (2018). Ordnance Survey (Digimap Licence)

The interventions are located on four publicly accessible sites; the total size of the floor area of green space in each of the intervention sites is small, ranging from 0.09 to 0.35 acres. Components of the interventions include tree and flower planting (expected to bloom by March 2018) and artificial tree decorations such as strings of small electric lights and tree socks (the interventions are hereafter collectively referred to as urban street greening). The total cost for all components across all four intervention sites is approximately £6000, although this excludes artist fees connected to the project. All components of the interventions were implemented within a 1 week period in November 2017 by two arborists, two local artists, staff members at Southway Housing Trust, and local community members from Old Moat and a local school. The Neighbourhood Green Space Tool (NGST) [46], a UK validated environmental audit tool for measuring the quality of green space, will be used to measure the environmental changes at the intervention sites.

A description of the key characteristics and locations of all intervention and comparison sites can be found in Table 1 and Fig. 5 respectively. An example of one of the intervention sites and one of the corresponding comparison sites at baseline are shown in Fig. 6.

**Table 1 Tab1:** Key characteristics of all intervention and comparison sites

Intervention and comparison sites	Location (postcode)	Intervention components	Floor area of green space (acres)	LSOA^a^	Population density (persons Haˉ^1^)^b^	Intersection density (per 1000mˉ^2^)^c^	IMD^d^	NDVI^e^	WalkScore^f^
Intervention site 1	M20 3GB	2 planted trees; bulb planting	0.09	Manchester 038C	79.50	15.37	23.08	0.38	94
Comparison site 1A	M19 1EN	–	0.05	Manchester 034B	82.58	16.13	29.87	0.47	71
Comparison site 1B	SK2 6DS	–	0.21	Stockport 019D	69.92	16.18	18.02	0.40	63
Intervention site 2	M20 1FU	12 planted trees; bulb planting; artificial tree decorations (string lights)	0.27	Manchester 038A	69.77	15.54	36.84	0.37	90
Comparison site 2A	M20 6FE	–	0.24	Manchester 040A	69.85	14.27	38.24	0.44	83
Comparison site 2B	OL6 8HH	–	0.14	Tameside 004C	73.19	16.68	51.14	0.46	54
Intervention site 3	M20 1GF	3 planted trees; artificial tree decorations (string lights, tree socks)	0.22	Manchester 035A	80.88	15.52	47.92	0.46	92
Comparison site 3A	M22 9PS	–	0.12	Manchester 050D	78.94	17.36	54.98	0.40	80
Comparison site 3B	OL6 8HW	–	0.19	Tameside 004C	73.19	16.68	51.14	0.46	63
Intervention site 4	M20 1AQ	8 planted trees; bulb planting; artificial tree decorations (string lights, tree socks)	0.35	Manchester 035A	80.88	15.52	47.92	0.46	48
Comparison site 4A	M22 9SZ	–	0.17	Manchester 050D	78.94	17.36	54.98	0.40	82
Comparison site 4B	M22 9PU	–	0.13	Manchester 050D	78.94	17.36	54.98	0.40	75

^a^Lower Layer Super Output Area (LSOA): census reporting units containing between 1000 and 3000 individuals

^b^Population density: number of persons per hectare; used as a proxy measure of residential density

^c^Intersection density: the number of 3-way junctions standardised by LSOA area; used as a measure of street connectivity

^d^Index of Multiple Deprivation Score (IMD) [45]: an area deprivation score that combines several indicators of deprivation including income, employment, health and crime. Higher scores indicate more deprived areas

^e^Normalised Difference Vegetation Index (NDVI): a validated normalised scale of healthy vegetation cover; used as a measure for presence of greenery at the neighbourhood-level. Higher scores indicate areas with more healthy vegetation cover

^f^WalkScore uses a Google search algorithm to calculate a weighted score (1–100) based on the number and accessibility of amenities (such as shops and parks) within a 1-mile radius of a user-entered postcode, whereby closer amenities with the most accessible walking routes are weighted more strongly; used as a measure of ‘access to/ availability of destinations and services’. Higher scores indicate more ‘walkable’ areas

**Fig. 5 Fig5:**
[figure not shown]
Map showing the location of all intervention and comparison sites in Greater Manchester. The numbers/ letters refer to intervention and comparison sites e.g. ‘1’ is Intervention site 1, and ‘1A’ and ‘1B’ are the corresponding comparison sites: Comparison site 1A and Comparison site 1B, respectively. See Table 1 for details on each intervention and comparison site. © Crown Copyright and Database Right (2018). Ordnance Survey (Digimap Licence)

**Fig. 6 Fig6:**
[figure not shown]
Intervention site 1 (top) and Comparison site 1A (bottom) at baseline. Photographs taken by [name]

### Logic model

Hypothesised causal pathways are outlined in the logic model (Fig. 7), which is based on the framework suggested by Panter et al. [47]. It is proposed that improvements in the aesthetic quality of green space will increase overt appreciation in the intervention sites. The interventions are hypothesised to influence only one known variable associated with physical activity: aesthetic quality of the route. More aesthetically pleasing streetscapes, including the presence of attractive and well-maintained trees and greenery, are valued by older adults in facilitating physical activity [37]. The artificial tree decorations (e.g. tree socks) will be present all year round, ensuring the presence of the intervention in colder seasons.

**Fig. 7 Fig7:**
[figure not shown]
Urban street greening logic model

#### Confounders

##### Weather

Observations will be carried out regardless of weather conditions, unless weather conditions become so extreme that they compromise the observer’s safety. To control for the confounding influence of weather, the observer will record the duration of any precipitation that occurs during each observation period. These data will inform a sensitivity analysis.

##### Other known confounders

Data collection at all time points will be carried out during UK school term dates to control for the change of activity around school holidays. Data collection is planned so that it does not overlap with the daylight saving clock change on 25th March 2018. A liaison from Southway Housing Trust will be contacted before data collection at each time point to enquire about any unrelated significant events that could influence the outcomes, such as other unrelated planned changes to the built environment. Media outlets (e.g. Twitter) will also be monitored to check for any significant events near to sites during data collection periods at each time point. Where possible, data collection will be arranged so that it does not co-occur with any unrelated significant events.

### Analysis plan

#### Inter-rater reliability

High inter-rater reliability for MOHAWk has previously been established between pairs of observers across three studies for assessing people’s behaviours and their characteristics (ICCs > 0.8) [33]. Inter-rater reliability will be calculated between each pair of observers at each time point to assess agreement on demographic and activity categories. Inter-rater reliability will be analysed using single rater two-way random effects ICC and percentage agreement.

#### Main analysis

The analysis will estimate the effect of the intervention on the number of older adults using the site at each of the two time points, and the types of behaviours they engage in per observation period, compared to the two corresponding comparison sites. The analysis will control for known confounders including weather, day and time. The primary analysis will analyse data for older adults and a secondary analysis will analyse data for all adults using the same methods.

The primary outcome will be a count per observation period of Take Notice behaviour at 12 months. Take Notice behaviour is the primary outcome because the interventions are expected to improve the aesthetic quality of green space by providing visual information of value to users, thus causing more overt appreciation in the intervention sites. The secondary outcome will be the overall count of older adults per observation period. Additional exploratory analyses will assess a count per observation period separately for each physical activity level (Sedentary, Walking, Vigorous) and Connect behaviour.

For each outcome we will follow three steps. Firstly, using a dataset that only includes the baseline data, and is blinded to group allocation, we will build a regression model to examine the relationship between the baseline count outcome and the covariates (weather, day, time). The overall count of older adults per observation period will be used as an additional covariate when analysing each of the behaviours (i.e. Sedentary, Walking, Vigorous, Take Notice, Connect). We will consider this count outcome as either a poisson distribution, a zero-inflated poisson or a normal distribution. We will consider all these approaches, and we will choose the most suitable approach by seeing which model has the best fit, assessed using Akaike’s information criterion (AIC) and measures of over-dispersion. Secondly, once we have developed a suitable model with the baseline data, we will combine the pre- and post-intervention data together and apply the model from step one. Thirdly, we will add into the model Group (intervention or comparison) and Period (pre or post). The treatment effect will be the coefficient for the interaction of Group and Period. This is a form of Difference in Differences analysis [48, 49], adapted because we do not have a before and after measure at the level of the hour.

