A power calculation showed that if we match four intervention sites and eight comparison sites (12 in total) and have eight observation periods per cluster, we will have 99% power (*p* = .05, two-tailed test) to detect a difference between 0.5 (SD = .77) counts per observation period of Take Notice behaviour in older adults in the control group and 1.6 (SD = 1.72) in the intervention group. This assumes the ICC is 0.02, *p* = .05, two-tailed test: this low ICC value has been used in previous studies that have evaluated homogeneous parks ([name], personal communication). This also assumes that the ‘comparison’ group and ‘intervention’ groups from the feasibility study accurately represent the comparison and intervention sites in the main study at follow-up. However, due to the lack of data from previous studies on changes in older adult’s Take Notice behaviours in urban street greening interventions, data from the feasibility data was the most suitable available data to inform the power calculation.

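### Choosing the outcome distribution from a baseline model without site can push the overall older-adult count towards a normal model and cost that secondary analysis power

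*Protocol article*

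**What the plan says.** The Main analysis section sets out three steps for each outcome.

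- **Step one** uses baseline data only, blinded to group: "we will build a regression model to examine the relationship between the baseline count outcome and the covariates (weather, day, time". For the behaviours, including the primary outcome Take Notice, there is one more term: "The overall count of older adults per observation period will be used as an additional covariate when analysing each of the behaviours". The candidates are "either a poisson distribution, a zero-inflated poisson or a normal distribution", judged by Akaike's "information criterion (AIC) and measures of over-dispersion".
- **Step two** carries the result forward: "we will combine the pre- and post-intervention data together and apply the model from step one".
- **Step three**: "we will add into the model Group (intervention or comparison) and Period (pre or post", with their interaction as the treatment effect.

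No step lists site or matched set. The Power calculation section, by contrast, treats the 12 sites as clusters of eight observation periods with an ICC of 0.02.

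**The concern.** Counts that are exactly Poisson within each site look over-dispersed once sites with different means are pooled without a site term. The candidate list has no over-dispersed count model such as the negative binomial, so the excess spread can only favour zero-inflated Poisson or normal. The choice is then fixed, and nothing later revisits it.

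The overall older-adult count is the exposed outcome, because it has no covariate that stands in for how busy a site is. If the normal model is chosen and site stays out, stable differences between sites remain in the residual variance although they cancel from the difference in differences. The standard error is then too large and real effects are missed.

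**Working it through.** **The plan's own figure.** The only design figure is 99% power for Take Notice, and this point does not rest on it. With the stated means and SDs, 4 v 8 sites, eight periods each and a design effect of 1 + 7 × 0.02 = 1.14, the variance of the difference is 1.14 × (0.77²/64 + 1.72²/32) = 0.116. Then z = 1.1/0.341 = 3.23, and power is about 90% with no matching correlation. Reaching 99% needs a correlation of about 0.43 on this calculation. The value used is not stated, so 99% can be neither confirmed nor refuted.

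**Inputs.** From the protocol: 12 sites × 8 periods = 96 baseline records; 4 intervention and 8 comparison sites; the three candidate distributions; ICC 0.02. Assumed, because the protocol gives no figure: a mean overall count of 6 to 12 per hour, the between-site CV, and the time-of-day effects.

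**Apparent over-dispersion from pooling.** For counts Poisson within site with mean m, pooled variance/mean = 1 + m × CV², and ICC = m × CV²/(1 + m × CV²).

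| m | CV | variance/mean | ICC |
|---|---|---|---|
| 6 | 0.15 | 1.14 | 0.12 |
| 6 | 0.3 | 1.54 | 0.35 |
| 6 | 0.5 | 2.50 | 0.60 |
| 12 | 0.3 | 2.08 | 0.52 |
| 12 | 0.5 | 4.00 | 0.75 |

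At ICC 0.02 the ratio is 1/(1 − 0.02) = 1.02, which is practically Poisson.

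**Which model AIC picks for the overall count** (simulated, truly Poisson within site, means 6-12):

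- CV 0.3: normal in 13-77% of baselines without site.
- CV 0.5: normal in 74-100% without site.
- With site in step one, at either CV: normal in 1-11%.
- CV 0.15 or ICC 0.02: a site term brings no improvement.

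The result depends on the setting. With an assumed rain effect added, a mean of 5 and ICC 0.35 (CV = √(0.35/(0.65 × 5)) = 0.33), the drift was to zero-inflated Poisson (29% without site, 5% with) and normal was picked in only 2%. At a mean of 10 and the same ICC (CV 0.23), normal was picked in 19% without site and 17% with.

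**Take Notice with the planned covariate.** Zero-inflated Poisson is picked in about 5-6% of runs when sites differ in usage. It rises only when sites differ in the propensity of users to take notice: 9-12% at ICC 0.20, 33-39% at ICC 0.35, and up to 55% at the largest spread tried (CV 0.74). Even then the rate ratio moves by at most about 10%.

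**Power for a 1.3-fold rise in the overall count, m = 6, CV = 0.5, by hand.**

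- Design factor: 2 × (1/32 + 1/64) = 0.09375.
- Normal model, no site: residual variance 6 + 6² × 0.5² = 15, so the reported SE is √(15 × 0.09375) = 1.19 and significance needs an estimate above 1.96 × 1.19 = 2.32. The true effect is 0.3 × 6 = 1.8. The estimate's actual SD is √(0.75² + 0.45²) = 0.87, where 0.75 = √(6 × 0.09375) is Poisson noise and 0.45 = 1.8 × 0.5/√4 comes from which four sites are treated. Power ≈ P(Z > 0.60) = 27%.
- Poisson model: log 1.3 = 0.262; variance 1/249.6 + 1/192 + 2/384 = 0.0144; SE 0.120; z = 2.18. Power ≈ 59%.

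Simulation gives about 30% against 63% in this setting. Across means 6-12 and CV 0.3-0.5 it gives 30-70% for normal without site, against 60-89% for Poisson or with site terms.

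**False positives.** With stable site effects and no treatment effect, the normal model as written rejects in 0-7% of runs, including under a common 40% fall. If site effects are added only at step three to a normal model, a common 40% fall gives 9-26%, while Poisson stays at 4-6%. A common 15% fall gives about 5-9% with the normal model.

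**The case against.** The strongest case on the other side has five parts.

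1. *At the protocol's own ICC of 0.02 nothing goes wrong.* This stands. But 0.02 is taken from evaluations of homogeneous parks, and Table 1 shows floor areas from 0.05 to 0.35 acres and WalkScores from 48 to 94, so a larger spread in usage is not excluded.
2. *The overall-count covariate protects the primary outcome.* This largely stands. A reader might infer that Take Notice will be given zero inflation that does not exist. That does not follow for the planned model unless sites differ strongly in propensity.
3. *The two feasibility sites do not measure spread among matched sites.* This stands. The control value "0.5 (SD = .77) counts per observation period of Take Notice behaviour" and the 1.6 at the other site give a CV of 0.778/1.05 = 0.74 and an ICC of roughly 0.25-0.37. But these are only two unmatched sites, and the second stood in for the intervention condition because it had benches and more greenery. The protocol's SDs, although upper confidence limits, also leave room for genuine over-dispersion within site (variance/mean 1.19 and 1.85).
4. *Type I error is not inflated.* This stands for the plan as written when site effects are stable. A reader might infer that seasonal change would appear as a treatment effect. That needs three things together: a normal model chosen without site, site effects added only at step three, and a large common fall. It bears on the February/March wave, not on the 12-month primary time point, which is in the same season as baseline. With sites matched closely on usage (assumed residual CV of 15%), rejection at a 40% fall is only 3-5%.
5. *Only AIC was simulated, while the plan also uses over-dispersion measures.* True. Those measures would read the same pooled spread as over-dispersion, so they give no protection.

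**Conclusion.** The point holds conditionally. Step one cannot separate between-site differences from a non-Poisson distribution, and no later step corrects the choice. If sites differ in usage by a CV of about 0.3 or more, the overall-count analysis may be moved to a normal model. As written it would then be conservative and underpowered, with roughly 30-70% power where 60-89% was available for a 1.3-fold rise.

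These sizes rest on assumed means, CVs and a 1.3-fold effect, on site effects that are stable over time, and on sites drawn independently rather than matched. The documents do not support saying that the wrong distribution will be carried forward, that the primary result is materially distorted, or that the plan as written inflates false positives through this route.

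The absence of site from the step-three model is a separate and weightier matter. With site-by-period variation (ICC 0.1), all three distributions rejected too often (15%, 12% and 9%), whichever was chosen.

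**What to change.** In step one, enter the 12 sites as scrambled codes with group still withheld, choose the distribution conditional on those codes for every outcome, and keep the same site terms in steps two and three. Adding site only at step three is not a safe substitute, for the reason given in the fourth objection.

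The cost is one sentence in the analysis plan and 11 of the 96 baseline degrees of freedom. Group blinding is preserved. There is one small side effect: when sites hardly differ (ICC 0.02), including site made AIC pick normal somewhat more often for the overall count (18% against 5% at an assumed mean of 5; 25% against 15% at a mean of 10). An additive model does little harm there, because the site means are nearly equal.

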### Research aim and objectives

The overall aim of this natural experimental study is to investigate the effect of planned changes in urban green space on older adults’ physical activity and wellbeing. The specific objectives are as follows:To examine whether small-scale urban green space interventions increase older adults’ Take Notice behaviour in comparison to matched comparison sites where no such changes occur (primary outcome). The primary outcome is Take Notice behaviour due to largest effects on this behaviour being anticipated from improvements in the aesthetic quality of green space at the intervention sites;To examine whether small-scale urban green space interventions increase the number of older adults’ using the intervention sites in comparison to matched comparison sites where no such changes occur (secondary outcome);To examine whether small-scale urban green space interventions increase older adults’ physical activity levels (sedentary, walking, vigorous activity) or Connect behaviour in comparison to matched comparison sites where no such changes occur (exploratory outcomes).

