### Greening interventions

The following descriptions are in line with the Template for Intervention Description and Replication (TIDieR) checklist [40].

This study is set in GM; a large metropolitan county in North West England with a population of around 2.8 million and containing ten metropolitan boroughs. GM is undergoing rapidly increasing urbanisation. As a result, integrating green space into this highly urbanised county is becoming a political priority for GM [41]. GM is therefore a strong case study for evaluating the effects of changes in urban green space on physical activity and wellbeing.

This study will evaluate four urban green space interventions designed and implemented by Southway Housing Trust: a housing association in GM. Southway Housing Trust state that the aim of the interventions is to increase the number of people actively using specific areas targeted for environmental improvements and improve wellbeing in the local community ([name], personal communication). The intervention sites are located in Old Moat (Fig. 4): a suburban ward with a population of 14,657 located in the city of Manchester. The population of Old Moat ward is relatively young compared to other wards in Manchester, although there are a high proportion of older adults living in Southway Housing Trust properties [42]. Manchester is ranked as the fifth most deprived local authority in England [43] and Old Moat is ranked as the 22nd most deprived ward in Manchester out of 32 wards [44] (based on the Index of Multiple Deprivation (IMD) Score [45]).

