### Power calculation

Given the lack of previous studies of the causal effects of urban street greening, it is difficult to estimate the plausible size of the effect that interventions will have on the outcomes. However, the interventions only target one known variable that can influence physical activity and wellbeing within the context of a broader complex ‘system’ [50]; therefore, the effects on the measured outcomes, particularly physical activity, are likely to be small.

To assess the power of the study, we conducted a power calculation of the primary outcome measure: counts per observation period (hour) of Take Notice behaviour in older adults. We used the approach suggested by Donner and Klar ([51], p.66) for calculating the sample size for a matched pair design: calculate the number of clusters required for a completely randomised cluster design, and then multiply that by one minus the correlation between the mean outcomes in the two groups. This suits our context because it allows us to account for multiple comparison groups for each intervention group. We used the means and standard deviations (SD) from the two sites in the feasibility study. We assumed that one site was the ‘comparison’ group (i.e. the intervention site at baseline) and the other site was the ‘intervention’ group (this site had two benches, more greenery and was thus more aesthetically appealing based on ratings using the NGST). For the SDs for each site, we used the 80% upper one-sided confidence limit of the SD to account for the possibility that the SD from the feasibility data may be an underestimate.

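### The primary Take Notice model adjusts for the concurrent number of older adults, so it does not estimate the unconditional count named in the outcome, objective and power calculation

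*Protocol article*

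**What the plan says.** The Main analysis section fixes the outcome as a count: "The primary outcome will be a count per observation period of Take Notice behaviour at 12 months". The power calculation uses the same scale, "counts per observation period (hour) of Take Notice behaviour in older adults". Objective 1 asks whether Take Notice behaviour increases and carries no per-user qualifier.

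The same section requires a further covariate for each behaviour, and its list names Take Notice: "The overall count of older adults per observation period will be used as an additional covariate when analysing each of the behaviours". That variable is itself an endpoint: "The secondary outcome will be the overall count of older adults per observation period". Objective 2 is worded "To examine whether small-scale urban green space interventions increase the number of older adults", and the Greening interventions section gives the provider's aim as to "increase the number of people actively using specific areas targeted for environmental improvements".

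The model is first built on baseline data, blinded to group. Then "we will combine the pre- and post-intervention data together and apply the model from step one", Group and Period are added, and "The treatment effect will be the coefficient for the interaction of Group and Period". The only sensitivity analysis described removes observation periods with prolonged precipitation.

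**The concern.** Because the baseline-built model is applied to the pooled data, the older-adult count enters the follow-up periods with its follow-up values. Building the model blind to group does not change that. The covariate is then a possible consequence of the intervention and lies on one route to the outcome: if more older adults use a site, more of them can be seen taking notice.

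Holding the count fixed blocks that route. The coefficient labelled as the treatment effect answers whether those present notice more. The stated outcome and objective ask whether there is more noticing at the site. These are different estimands, and they differ by exactly the change in use that objective 2 sets out to test. If use rises, the primary result understates the total effect and the planned test has less power than the unadjusted comparison. With no unadjusted result planned, a reader could not see the gap.

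**Working it through.** **Step 1. The plan's own figure.** Inputs from the Power calculation section: means 0.5 (SD 0.77) and 1.6 (SD 1.72); 4 and 8 sites with 8 periods each, so 32 and 64 periods; ICC 0.02; two-sided 0.05.

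- Design effect: 1 + (8 − 1) × 0.02 = 1.14.
- Weighted pooled variance: (31 × 1.72² + 63 × 0.77²) / 94 = 1.373.
- Standard error: √[1.14 × 1.373 × (1/32 + 1/64)] = 0.271.
- Power: Φ(1.1 / 0.271 − 1.96) = Φ(2.10) = 98.2%, against a stated 99%.

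A simple average of the variances gives 94.6%, and separate variances give 89.8%. Reaching 99% needs a matching correlation of about 0.10, 0.31 or 0.43 under the three conventions. The method uses such a correlation, but its value is not given. The stated figure is therefore attainable. It compares raw counts, and nothing in it conditions on the number of users.

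**Step 2. What the covariate does.** Write the expected Take Notice count as users × share noticing. If the intervention multiplies users by k and the share by r, the count is multiplied by k × r. The planning values give k × r = 1.6 / 0.5 = 3.2. A model that fully accounts for the number of users targets r = 3.2 / k:

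- k = 1: 3.2
- k = 1.1: 3.2 / 1.1 = 2.91
- k = 1.2: 3.2 / 1.2 = 2.67
- k = 2: 3.2 / 2 = 1.6
- k = 3.2: 3.2 / 3.2 = 1.0

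**Step 3. Simulation.** Assumptions not in the article: 10 older adults per period in the absence of an effect, a 5% share noticing (10 × 0.05 = 0.5), Poisson numbers of users, no site clustering. Design: 12 sites, 8 periods, pre and post. Poisson difference-in-differences models were fitted with and without the concurrent count. The total rise is 3.2-fold in every row.

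| Change in users | Rate ratio, without count | Rate ratio, with count | Power, without | Power, with |
|---|---|---|---|---|
| none | 3.3 | 3.3 | 0.9 | 0.9 |
| +10% | 3.2 | 2.9 | 0.9 | 0.8 |
| +20% | 3.3 | 2.7 | 0.9 | 0.75 |
| doubled | 3.2 | 1.5 to 1.6 | 0.9 | 0.15 to 0.2 |
| ×3.2 (whole rise) | 3.3 | 1.0 | 0.9 | about 0.05 |

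These powers come from a log-scale interaction that also uses the baseline data, so they should be compared across columns and not with the stated 99%.

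**Step 4. Sensitivity to the model chosen.** Under a normal model with the whole rise through use, the difference of 1.1 falls to about 0. With 8 older adults per period and extra between-period variation, the Poisson ratio falls to 1.26 if the count enters linearly and to 1.01 if it enters on the log scale. The conclusion does not depend on which of these forms is selected.

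**The case against.** The strongest reply is that behaviour among users is what the authors want. The Main analysis section separates how many older adults use the site from what they do there. The rationale for the primary outcome, and the Logic model section, describe a direct route from better aesthetics to more visible appreciation. Use then has its own test as the secondary outcome. This has some support, and a per-user effect is a legitimate target. But it is never stated as the estimand, and the outcome definition, objective 1 and the power calculation all use the unconditional count. If it is intended, those parts need correcting instead.

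A second reply is that use may hardly change. The sites are small, only aesthetic quality is targeted, and the Power calculation section expects small effects. This stands as a limit on size: with no change in use the two models agree in both estimate and power.

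Third, the study is not randomised. All four intervention sites lie in one ward, while the comparison sites are spread more widely. A local shift in use unrelated to the greening would enter an unadjusted count and look like an effect. This also stands. It argues for showing both analyses, not for keeping only the adjusted one.

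A reader might go further and infer that the primary analysis is bound to miss a real effect. The article does not support that: near-total loss requires nearly all of the rise to come through use, and no expected change in use is given. A reader might also infer that the count enters as a linear term in a log-link model, or that Walking adjusted for the total is almost constant because 95% of those present walk. The article states no functional form, leaves a normal model open and gives no activity distribution. Both are assumptions, and the point does not rest on them.

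**Conclusion.** The point holds as a mismatch between the stated primary outcome and the planned primary model. The article itself fixes the covariate, so this is not a detail left to a statistical analysis plan. The planned coefficient excludes any effect of the greening that works through greater use, and no planned Take Notice analysis recovers it.

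The size runs from nothing, if use is unchanged, to the whole effect, if the rise comes entirely through use. For changes in use of 10 to 20% the rate ratio falls from about 3.3 to between 2.9 and 2.7, and power from about 0.9 to between 0.8 and 0.75. These values rest on the assumed 10 users per period, the 5% share, the planned 3.2-fold total rise and no clustering. The direction of the shortfall when use rises follows from the structure of the model.

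The 99% power figure is not shown to be wrong. It belongs to the unadjusted comparison and carries over to the adjusted one only if use does not change materially.

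**What to change.** Make the Take Notice model without the concurrent older-adult count the primary analysis, keeping weather, day and time. This matches the outcome as defined and as powered. Beside it, report a labelled per-user analysis, either with the log of the older-adult count as an offset or as Take Notice out of those observed, described as the effect on behaviour among those present. Do the same for the exploratory Connect and physical activity outcomes.

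This changes a sentence or two of the analysis plan and needs no new data. It may cost some precision by leaving variation in use unexplained, although in the simulation with unchanged use the power was the same with and without the covariate. The larger cost is that shifts in use unrelated to the greening enter the unadjusted count. Both results should therefore be shown and read together with the secondary outcome.
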